## Introduction

1

Acute respiratory distress syndrome (ARDS) is a common clinical disease characterized by acute hypoxemia, decreased lung compliance, and non-cardiogenic pulmonary edema, which can cause a series of serious complications and even progress to multiple organ failure.^[1–4]^ ARDS can be attributed to a variety of factors, including sepsis, multiple injuries, massive blood transfusions, pneumonia, aspiration, and lung contusions, among others. The primary pathophysiological feature of ARDS is the accumulation of a large amount of protein-rich fluid in the alveolar space due to damage of the diffuse alveolar capillary barrier.^[5–7]^ Although comprehensive studies have provided clinicians with a better understanding of the complex pathogenesis of ARDS, the incidence rate is still increasing.^[8,9]^ There is evidence that the mortality rate of ARDS patients is as high as 30% to 40% and is therefore an important cause of death in critically ill patients.^[10–15]^ Despite more than 50 years of research, there is still no specific treatment designated for ARDS, with options limited to supportive care, including protective mechanical ventilation and restriction of fluids,^[16]^ Therefore, finding more effective prevention and treatment strategies for ARDS is an urgent concern.

Traditional Chinese medicine (TCM) characteristically takes a holistic view and differentiates syndromes and treatments, potentially offering advantages and supportive effects in the management of ARDS. There is no record of a disease called ARDS in TCM. However, according to the patients’ clinical symptoms, such as shortness of breath, high fever, dry stools, crimson tongue, and the number of pulse slips, it would be diagnosed as “asthma syndrome.” The syndrome can be subdivided into “asthma syndrome” (early) and “asthma syndrome” (late). The prescriptions determined through syndrome differentiation and treatment has played a role in the diagnosis and treatment of ARDS, laying a foundation for Chinese medicine to participate in its treatment. Chinese medicine has a wide range of mechanisms to treat ARDS, mainly by regulating the cytokine network; protecting endothelial function; through antioxidation; regulating the coagulation/fibrinolysis system, immunity, and water; and through sodium transport.^[17]^

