### Sample size

2.4

Calculating the sample size was based on the effective rate. According to previous research, the effective rate for the treatment group with integrated traditional Chinese and Western medicine is 65.2%, and effective rate for the group with Western medicine alone is 34.8%. The software Power Analysis and Sample Size version 11.0 (PASS 11.0)was used to calculate the sample size of the 2 groups, assuming that 10% of patients are likely to be lost during follow-up, a total of 110 patients will be enrolled.

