**Table 3 T3:**
[figure not shown]
Quantitative standard for the classification of symptoms and signs.

The criteria for determining the therapeutic effect of TCM will be formulated in accordance with the guiding principles for clinical research for new TCM drugs^[25]^ (Trial) and the criteria for the therapeutic effect of the diagnosis of diseases and syndromes of TCM issued by the Chinese Society of TCM.

(1)Cure: the clinical symptoms and signs disappear or basically disappear, and the laboratory examination reveals visible improvement. The TCM syndrome score is reduced by more than 95%.(2)Significant effect: the clinical symptoms, signs, and laboratory tests are significantly improved. The TCM syndrome score is reduced by ≥70%.(3)Effective: the clinical symptoms, signs, and laboratory tests are improved. The TCM symptom score is reduced by ≥30%.(4)Invalid: the clinical symptoms and signs are not improved or have worsened. There is a < 30% reduction in the TCM symptom score.

2. PɑO2/FiO2: before and after the intervention, we will perform arterial blood gas analyses to measure changes in the PɑO2/FiO2.

3. Extravascular pulmonary water index: will be obtained from the PiCCO monitor (It is a tool to detect the main hemodynamic parameters of severe patients)

4. Length of time with ventilator: the time with the ventilator will be 14 days from the patient participating in the trial to the treatment.

5. ICU length of stay: the actual length of stay = date of leaving the ICU - date of entering the ICU + 1.

6. 28-day mortality: the mortality rate from the beginning of the trial to the 28th day will be recorded.

7. Follow-up records: During the follow-up period, the all-cause mortality, respiratory failure mortality, and readmission rate in the 1-year period after discharge will be recorded. Criteria for readmission: subjects readmitted for ARDS or other respiratory diseases, not including any other disease or reason. If readmission occurs during the follow-up period, the readmission rate will not be recorded during the follow-up period. Readmission rate = number of patients readmitted/number of patients who completed follow-up.

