### Statistical analyses

3.7

Before analysis, 2 similar participants with complete data will be carefully examined to ensure that the data is correct. All data analyses will then be based on treatment intention.

The data will be analyzed using the statistical software package SPSS 22.0 (Chicago, IL). The analysis method will be selected according to the distribution characteristics of the data. The measured data will be expressed as the mean ± the standard deviation. First, the normal test and the homogeneity test of variance will be performed. In the case of normal distribution and equal variance, a *t*-test will be performed; otherwise, a nonparametric test will be utilized. The difference will be statistically significant when *P* ≤ .05.

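### ICU stay and ventilator time are raw durations that do not separate recovery from death, so an arm with more early deaths can look better on both

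*Protocol article*

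**What the plan says.** The outcomes are in Section 3.2 (Determination of results).

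- **ICU stay (item 5):** "the actual length of stay = date of leaving the ICU - date of entering the ICU + 1".
- **Ventilator time (item 4):** "the time with the ventilator will be 14 days from the patient participating in the trial to the treatment". The sentence is garbled. The natural reading is time on the ventilator within the two-week treatment period.
- **Mortality (item 6), a separate outcome:** "the mortality rate from the beginning of the trial to the 28th day will be recorded".

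On analysis, Section 3.7 says of measured data: "In the case of normal distribution and equal variance, a *t*-test will be performed; otherwise, a nonparametric test will be utilized". It also says "All data analyses will then be based on treatment intention" and "The difference will be statistically significant when *P* ≤ .05".

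On background risk, the Introduction says that "the mortality rate of ARDS patients is as high as 30% to 40" percent. Nowhere does the article say how a death enters either duration.

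**The concern.** Under the item 5 formula, a patient who enters the ICU on day 1 and dies there on day 3 has a stay of 3 - 1 + 1 = 3 days. A patient who recovers and leaves on day 3 has the same value. The comparison reads a shorter stay as a better result, so the death counts as one of the best outcomes. The nonparametric fallback does not cure this, because it ranks the early death among the shortest stays.

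Deaths would not be rare. At the cited mortality, 110 patients would include 0.30 × 110 = 33 to 0.40 × 110 = 44 deaths. Section 3.2 says that no single index suffices and that the disease must be evaluated as a whole, so these two durations form part of the efficacy evidence. What is at stake is a shorter mean stay being read as benefit when part of it comes from excess deaths, or a real survival benefit being offset by longer stays.

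**Working it through.** **The plan's own figure.** The article gives no numerical assumption for either duration. Its one design figure, 110 patients, rests on effective rates of 65.2% and 34.8% (Section 2.4). With two-sided alpha 0.05, power 80% (both assumed) and a continuity correction, the two-proportion formula gives 48 per arm. Allowing for 10% loss, 48/0.9 rounds up to 54 per arm, or 108 in total, within 2 of the stated 110. Nothing below depends on this.

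**Inputs.** From the documents: the item 5 formula, the 14-day period, cited mortality of up to 30% to 40%, and 55 patients per arm (110 at 1:1). Assumed: 40% mortality in one arm and 30% in the other, and all distributions of stay.

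**Model A: survivors' stays identical in both arms.** Mean raw stay = (1 - m) × S + m × D, where m is mortality, S the survivors' mean stay and D the non-survivors' mean stay. Assume survivors are lognormal with median 14 days and log-SD 0.5, so S = 14 × exp(0.5²/2) = 15.86. Assume deaths are uniform over days 1 to 14, so D = 7.5.

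- 40% mortality: 0.6 × 15.86 + 0.4 × 7.5 = 12.52 days
- 30% mortality: 0.7 × 15.86 + 0.3 × 7.5 = 13.35 days

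The arm with 10 points more deaths looks about 0.8 day better. On ICU-free days to day 28 with death scored 0, it has 7.7 against 9.0, about 1.3 days worse.

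**How far the sign depends on the assumptions.** In Model A the difference is 0.10 × (D - S). With S = 14 days:

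| Non-survivors' mean stay D | 0.10 × (D - 14) | Simulated difference |
|---|---|---|
| 5 | -0.9 | -0.92 |
| 7 | -0.7 | -0.73 |
| 10 | -0.4 | -0.40 |
| 14 | 0 | -0.03 |
| 18 | +0.4 | +0.38 |

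**Model B: identical daily rate of leaving alive.** Let r be the constant daily rate of leaving alive and h the death rate, so eventual ICU mortality is m = h/(r + h) and mean raw stay = 1/(r + h) = (1 - m)/r. With r = 0.05 per day:

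- 40% mortality: 0.60/0.05 = 12.0 days
- 30% mortality: 0.70/0.05 = 14.0 days

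The arm with more deaths looks 2.0 days better. The ratio 0.60/0.70 = 0.857 holds for any r, and the gap runs from 1.0 day (r = 0.10) to 3.3 days (r = 0.03). In this model survivors and non-survivors of the same arm have equal mean stays by construction. The gap arises because a higher death rate removes patients who would otherwise have stayed longer.

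Mean days alive and out of the ICU to day 28 = (1 - m) × {28 - [1 - exp(-28(r + h))]/(r + h)}. At r = 0.05 this gives 10.30 against 11.13, so the arm with more deaths is 0.83 day worse. Over r = 0.03 to 0.10 it is 0.43 to 1.56 days worse.

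**Ventilator time, natural reading.** With r as the rate of coming off the ventilator alive, mean time capped at 14 days = [1 - exp(-14(r + h))]/(r + h). At r = 0.05 this is 8.26 against 8.85 days, so the arm with more deaths looks 0.59 day better. Over the same range of r the gap is 0.46 to 0.63 day.

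**Size against the trial's precision.** In Model A the survivor variance is 15.86² × (exp(0.25) - 1) = 71.4 and the non-survivor variance is 13²/12 = 14.1. The mixture variances are:

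- 40% mortality: 0.6 × 71.4 + 0.4 × 14.1 + 0.24 × 8.36² = 65.3 (SD 8.1)
- 30% mortality: 0.7 × 71.4 + 0.3 × 14.1 + 0.21 × 8.36² = 68.9 (SD 8.3)

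The standard error of the difference is √[(65.3 + 68.9)/55] = 1.56 days, so the artefact is about half a standard error. In Model B stays are exponential with SD equal to the mean. The standard error is √[(12² + 14²)/55] = 2.49 days, and the artefact is 2.0/2.49 = 0.8 standard error.

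**The case against.** The strongest case against has four parts.

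1. **Direction and size.** The direction is not fixed. With survivors' stays held equal between arms, it vanishes when non-survivors stay as long as survivors and reverses when they stay longer. The 40% versus 30% split is invented. The cited mortality describes ARDS patients in general, whereas this trial takes ages 20 to 70 and excludes several high-risk groups. All of this stands. It limits the claim to what can happen.

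2. **Visibility.** These are two of seven listed outcomes and the sample size rests on another. Mortality at 28 days and 1 year is reported separately, so a shorter stay with more deaths could be noticed. If the treatment lowers mortality, the artefact works against it. This stands too and lowers the severity. Separate reporting does not, however, correct the comparison of durations.

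3. **Analysis plan.** The handling of deaths is often left to an analysis plan, which is not shown. This does not remove the point, because the article itself fixes the ICU-stay formula. A death rule in that plan would, however, settle it.

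4. **Item 4.** A reader might infer that item 4 sets everyone's ventilator time to 14 days. The sentence is poorly worded, and the two-week treatment period supports the natural reading. It needs rewording, and the point is firmest for ICU stay.

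A reader might also infer bias from counting ICU stay from ICU entry. Randomisation balances any earlier days in expectation, so they add noise, not bias, and the article gives no lag from which to size it.

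**Conclusion.** The point holds in a conditional form. The ICU-stay formula, and ventilator time on its natural reading, do not distinguish recovery from death, and the planned comparison keeps patients who die. An arm with more early deaths can therefore look better on both outcomes when death shortens stays. Under an assumed 10-point mortality difference, the two main illustrations give about 0.8 to 2 days on mean ICU stay, and the second gives about 0.6 day on ventilator time. Of these inputs, only the 30% to 40% mortality range and the 14-day period come from the document.

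A reader might infer that the arm with more deaths will necessarily look better, or that a false positive result is likely. Neither is supported: the sign depends on how long non-survivors stay, and the ICU-stay artefact is roughly 0.5 to 0.8 of a standard error at 55 per arm. This should be fixed, but it does not undermine the trial's design, and the sample size of 110 is unaffected.

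**What to change.** - Replace items 4 and 5 as comparative outcomes with ventilator-free days and ICU-free days from randomisation to day 28. Score death by day 28 as 0 (worst rank) and compare arms by a rank-based analysis in all randomised patients. An acceptable alternative for ICU stay is time to leaving the ICU alive, with death as a competing event.
- Show 28-day mortality beside each result.
- Keep the raw durations as descriptive figures only, separately for survivors and non-survivors.
- Reword item 4 to state the ventilator observation window.

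**Cost.** Revised outcome wording, plus ventilator dates for days 15 to 28. ICU dates and 28-day vital status are already needed for items 5 and 6. The downside is small: the new outcomes are composites with mortality, which is why mortality must be shown alongside.

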### Design

2.1

This study is a prospective, multicenter, double-blind, randomized, placebo-controlled clinical trial. The center of research participation includes 4 medical institutions in China: The Affiliated Hospital of Chengdu University of TCM, The Meishan Hospital of TCM, The Neijiang Second People's Hospital, and The ICU of Suining Hospital of TCM.

The trial has been registered in the China Clinical Trial Registration Center (No. ChiCTR1900022693, which was submitted on April 23, 2019, Version.V1.4). After obtaining written informed consent, the 110 participants will be randomly divided into 2 groups at a proportion of 1:1. The 2 groups will be the integrated traditional Chinese and Western medicine treatment group and the Western medicine alone treatment group. The 2 groups of patients will receive 2 weeks of intervention treatment and 1 year of follow-up. The purpose of this experiment is to study the clinical effect of integrated traditional Chinese and Western medicine on patients with ARDS, and to evaluate the efficacy and safety of the JWQYD. At the same time, we will evaluate the long-term effect of adjuvant therapy with Chinese medicine and determine clinically effective treatments for ARDS patients. This study will follow the 2013 Standard Protocol Items: Recommendations for Interventional Trials (SPIRIT). Refer to Figure 1 for information about SPIRIT registration, intervention, and evaluation and Document 1 for the SPIRIT list.^[21]^ The study flow chart is shown in Figure 2.

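### The 1-year mortality outcomes start at discharge, so they compare patients discharged alive, and no outcome gives mortality from randomisation to 1 year

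*Protocol article*

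**What the plan says.** Section 3.2 of the protocol article (Determination of results) contains two mortality items with different starting points.

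- Item 6, 28-day mortality: "the mortality rate from the beginning of the trial to the 28th day will be recorded". The clock starts with the trial.
- Item 7, follow-up records: "the all-cause mortality, respiratory failure mortality, and readmission rate in the 1-year period after discharge will be recorded". The clock starts at each patient's discharge. Item 7 gives no denominator for mortality. The only one it gives is for readmission: "Readmission rate = number of patients readmitted/number of patients who completed follow-up".

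Three other statements bear on how item 7 should be read. Section 2.1 (Design) says "The 2 groups of patients will receive 2 weeks of intervention treatment and 1 year of follow-up" without giving the start of that year, and states the purpose: "we will evaluate the long-term effect of adjuvant therapy with Chinese medicine". Section 3.7 (Statistical analyses) says "All data analyses will then be based on treatment intention".

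**The concern.** Being discharged alive happens after randomisation and may depend on treatment. An outcome that can occur only after that event compares two groups that randomisation did not create. If the herbal preparation helped severely ill patients to leave hospital alive, its post-discharge group would include frailer people than the control group, and a real survival gain could vanish or reverse in item 7. If it did harm in hospital, item 7 would not show it.

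Discharge is also not a clean marker of recovery here. Section 2.9 lists leaving on request, transfer and giving up treatment for financial reasons among the grounds for withdrawal.

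What is at stake is the trial's only mortality evidence beyond day 28. The plan promises an evaluation of the long-term effect on an intention-to-treat basis, and item 7 as defined cannot deliver that for mortality.

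**Working it through.** **The plan's own figure.** The article states no figure for 1-year mortality. Its only design figure is the total of 110, set by the effective rate: section 2.4 says "the effective rate for the treatment group with integrated traditional Chinese and Western medicine is 65.2"%, against 34.8% on Western medicine alone. With two-sided 5% alpha, 80% power (both assumed, as neither is stated) and a continuity correction, this needs 48 per arm. Then 48 / 0.90 = 53.3, rounded up to 54 per arm, or 108 in total, within two patients of 110. Mortality plays no part in it, so this point leaves the sample size alone.

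**Where each death is counted, reading items 6 and 7 side by side.**

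| Death | Item 6 (28-day) | Item 7 (1-year) |
|---|---|---|
| In hospital, by day 28 | yes | no |
| In hospital, after day 28 | no | no |
| After discharge, by day 28 | yes | yes |
| After discharge, after day 28, within a year of discharge | no | yes |

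One type of death is in neither item and one is in both, so cumulative 1-year mortality cannot be obtained by adding the two.

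**How far the two definitions can differ.** Let h be in-hospital mortality and q the post-discharge mortality among those discharged alive. Then:

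- item 7, among patients discharged alive: q
- mortality from randomisation: h + (1 − h) × q
- post-discharge deaths divided by all randomised patients: (1 − h) × q

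For simplicity the second line runs to one year after discharge, slightly beyond one year after randomisation. All rates below are assumed; none comes from the documents as a rate for this trial.

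| Case (control / treated) | Item 7 | From randomisation | Post-discharge deaths / all randomised |
|---|---|---|---|
| A. h 40% / 30%; q 10% in both | 10% / 10% | 46% / 37% | 6% / 7% |
| B. as A, but the extra survivors on treatment have 40% post-discharge mortality | 10% / 14.3% | 46% / 40% | 6% / 10% |
| C. h 40% / 40%; q 10% in both | 10% / 10% | 46% / 46% | 6% / 6% |
| D. h 30% / 40%; q 10% in both | 10% / 10% | 37% / 46% | 7% / 6% |

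Arithmetic for A: control 0.40 + 0.60 × 0.10 = 0.46; treated 0.30 + 0.70 × 0.10 = 0.37. For B, treated: post-discharge deaths 0.60 × 0.10 + 0.10 × 0.40 = 0.10; item 7 = 0.10 / 0.70 = 0.143; from randomisation 0.30 + 0.10 = 0.40.

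In A a 9-point benefit disappears without assuming any extra frailty. In B a 6-point benefit becomes 4.3 points of apparent harm. In C the definitions agree. In D a 9-point harm disappears from item 7. The last column shows that putting all randomised patients in the denominator, without moving the start of the clock, does not cure the fault: in-hospital deaths then count as non-deaths, and the direction in A and D is wrong.

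**How many patients this could involve.** The Introduction says "the mortality rate of ARDS patients is as high as 30% to 40"%, a background figure with no time point. If it applied to in-hospital death in this trial, 110 × 0.30 = 33 to 110 × 0.40 = 44 patients would die before the item 7 clock starts, leaving 77 to 66 at risk. This is an illustration only.

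**The case against.** The strongest reply is that items 6 and 7 work as a pair. A reader might infer from item 7 that every in-hospital death is lost to the trial, or that a treatment causing early deaths would look good. The documents do not support either reading. Item 6 counts deaths from the start of the trial to day 28, so an early excess would count against the treatment there, and section 3.5 puts all adverse events in the case report file. This stands. What remains is narrower: in-hospital deaths after day 28 are in neither mortality outcome, and the two items cannot be combined into a cumulative figure.

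Second, item 7 is worded as a record and names no comparison or denominator for mortality, which a fuller document might supply. This is correct as far as it goes. The survivor comparison follows from the stated window, not from a stated denominator. But the window itself is stated, and no choice of denominator repairs it. If the discharge window were read as belonging to readmission alone, the mortality outcomes would have no stated starting point, and the same correction would be needed.

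Third, the 30% to 40% may not apply. It is an upper-end background figure, and section 2.8 excludes patients over 70, those with malignancy or organ dysfunction from severe disease, and those who may die within 12 hours of ICU entry. This stands, so a firm count of missing patients per arm cannot be claimed.

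Fourth, the particular survival methods are usually left to an analysis plan. This also stands. The request here concerns the time origin and the population; the method is only an example.

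**Conclusion.** The concern holds in limited form. By their stated window, the 1-year all-cause and respiratory-failure mortality outcomes exclude in-hospital deaths and so compare patients discharged alive. No outcome measures mortality from randomisation to 1 year. That conflicts with the treatment-intention principle in section 3.7 and the long-term aim in section 2.1.

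The size and direction of the bias are unknown. They depend on how far in-hospital mortality differs between the arms and on how frail the additional survivors are. Under the assumed rates above, the effect ranges from none (case C) to a hidden 9-point difference (A and D) or a reversed sign (B).

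A reader might go further and take this as a flaw in the trial's main result. The documents do not support that: these are follow-up outcomes, the sample size rests on the effective rate, and the efficacy rate and 28-day mortality are untouched. It should be fixed, but it is not a must-fix.

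**What to change.** In section 3.2, item 7, define 1-year all-cause mortality and 1-year respiratory-failure mortality from randomisation, with all randomised patients in the denominator. A time-to-event analysis would serve, for example, with death from other causes treated as a competing event for respiratory-failure death. Keep mortality after discharge as a descriptive figure only, and say that it describes patients discharged alive.

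The cost is small. For anyone discharged alive, one year after randomisation falls before one year after discharge, so the telephone follow-up in section 3.8 already spans the window. In-hospital deaths should already be in the case report file under section 3.5. The change is not purely one of wording, though: nothing in the article says that patients withdrawn under section 2.9 are followed for vital status. The plan should state that their status at 1 year will also be sought by telephone, subject to consent.

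### The 1-year readmission outcome has a recording rule that contradicts it and a denominator of undefined follow-up completers

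*Protocol article*

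**What the plan says.** All the relevant text on the outcome is in section 3.2, item 7 (follow-up records) of the protocol article. Four statements follow one another there:

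- The outcome and its window: "During the follow-up period, the all-cause mortality, respiratory failure mortality, and readmission rate in the 1-year period after discharge will be recorded".
- Which events qualify: "Criteria for readmission: subjects readmitted for ARDS or other respiratory diseases, not including any other disease or reason".
- The recording rule: "If readmission occurs during the follow-up period, the readmission rate will not be recorded during the follow-up period".
- The formula: "Readmission rate = number of patients readmitted/number of patients who completed follow-up".

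Two other places bear on the point. Section 2.1 (Design) fixes the length of follow-up: "The 2 groups of patients will receive 2 weeks of intervention treatment and 1 year of follow-up". Section 3.7 (Statistical analyses) sets the analysis principle: "All data analyses will then be based on treatment intention". I read this as intention to treat.

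The article does not say when a patient counts as having completed follow-up. In particular, it does not say whether a patient who dies during the year has done so.

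**The concern.** There are two separate defects in the same item.

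**Recording rule.** The item asks for readmissions in the year after discharge, and then says that a readmission in that period leads to no recording. Nothing else in the article reconciles the two. Four centres have to apply the rule, and each could do so differently: record nothing, record the first event only, or stop following a patient once readmitted. The last would also put that patient's 1-year mortality record at risk. Section 3.8 says follow-up status is obtained by telephone, and section 3.6 says locked data will not be changed. Events not recorded at the time may therefore be hard to recover, and an analysis plan written later could not restore them.

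**Denominator.** Dividing by completers makes the denominator depend on survival and retention after randomisation, while the numerator carries no stated matching restriction. If deaths or losses differ between arms, the readmission rates can differ even when the same number of patients is readmitted.

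**Working it through.** **Step 1: set the sentences side by side.**

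| Element | Content | Consequence |
|---|---|---|
| Outcome | Readmission within 1 year of discharge is recorded | Events in the year are needed |
| Recording rule | A readmission in follow-up means no recording in follow-up | Events in the year are not recorded |
| Formula | Patients readmitted divided by completers | Events in the year are needed again |

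The outcome and the formula need what the recording rule withholds. The three cannot all be followed. If the recording rule prevailed, the numerator would be 0 in both arms.

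**Step 2: is there a figure in the plan to reproduce?** None for readmission. The only sample size is 110 (section 2.4), based on effective rates of 65.2% and 34.8%. With two-sided 0.05, an assumed power of 80% and a continuity correction, this gives 48 per arm; 48/0.9 rounds up to 54, so 108 in total, close to 110. Readmission does not enter that calculation, so the total does not depend on this point.

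**Step 3: what the denominator does within one arm.** Only the arm size (110/2 = 55) comes from the document. Assumed: 36 of the 55 are discharged alive, which is about 65% (55 × 0.65 = 35.75) and corresponds to the midpoint of the 30% to 40% background mortality in the Introduction. Also assumed: 10 are readmitted, 5 of these die within the year, and nobody else is lost.

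- All discharged alive: 10/36 = 27.8%.
- Completers, deaths not counted as completing: 36 − 5 = 31, so 10/31 = 32.3%.
- Completers, deaths counted as completing: 10/36 = 27.8%.

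The denominator choice alone therefore moves this example by 32.3 − 27.8 = 4.5 percentage points, or by nothing, depending on an undefined term.

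Patients lost to follow-up drop out on any reading. If the 10% loss assumed in section 2.4 is applied to the 36, and the 10 readmissions are still known, the denominator is 36 × 0.9 = 32.4 and the rate is 10/32.4 = 30.9%, even with deaths counted as completing.

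**Step 4: what it could do between arms.** Assumed: 55 per arm, 10 readmitted in each arm, 10% of survivors lost, deaths not counted as completing, and 1-year mortality placed at the two ends of the Introduction's range.

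| Mortality, arm A / arm B | Completers A | Completers B | Rate A | Rate B | Difference, B − A |
|---|---|---|---|---|---|
| 30% / 40% | 55 × 0.70 × 0.9 = 34.65 | 55 × 0.60 × 0.9 = 29.7 | 28.9% | 33.7% | +4.8 points |
| 40% / 30% | 29.7 | 34.65 | 33.7% | 28.9% | −4.8 points |
| 35% / 35% | 55 × 0.65 × 0.9 = 32.2 | 32.2 | 31.1% | 31.1% | 0 |

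On all randomised patients the rate is 10/55 = 18.2% in each arm in every row. The between-arm difference comes only from the assumed mortality split. It changes sign when the split is reversed and vanishes when mortality is equal.

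**The case against.** The strongest reply is that the recording sentence is garbled wording rather than a plan to record nothing. The same item gives the window, the qualifying diagnoses and a formula, and the formula counts patients rather than episodes. That fits a rule under which repeat readmissions of one patient are not counted again. A reader might infer that the outcome is empty, with 0% in both arms by design, but this requires one sentence to override the others around it. The documents support a contradiction, not an intention to collect nothing. The contradiction stands, because the first-readmission reading is stated nowhere.

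On the denominator, the reply is that the term is undefined. All-cause mortality is an outcome of the same follow-up, so a patient followed to death might count as having completed it. That is fair: the exclusion of deaths is the ordinary reading, not a stated rule. The exclusion of patients lost to follow-up remains on any reading, and so does the tension with section 3.7.

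A reader might also infer that the readmission comparison is biased by a known amount, or that the patients who die are mostly those who were readmitted. The article supports neither. Every count in the illustrations is assumed, and the document says nothing on how deaths and readmissions overlap. Combining the literal 0% with the denominator effect into one range would mix two different defects.

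Finally, competing-risk methods are detail that an article may leave to an analysis plan. That is true, but the point here is a stated rule and a stated formula that do not work, not an omission.

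**Conclusion.** The point holds in two parts.

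1. The recording rule contradicts the outcome it belongs to. This follows from the text alone and needs no assumption.
2. The completers' denominator is undefined and selected after randomisation. It excludes at least the patients lost to follow-up and conflicts with the intention-to-treat statement. Whether it also excludes deaths depends on a definition that the article does not give.

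The size is illustrative only: 4.5 percentage points within one arm under the assumed counts if deaths are excluded. Between arms there is a risk of bias whose size and direction cannot be derived from the document.

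The grade is should-fix. Readmission is one of three 1-year measures in the last of seven outcome items, it did not drive the sample size, and no decision rule in the article rests on it. It still matters, because section 2.1 names the long-term effect of the adjuvant therapy as something the trial will evaluate.

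**What to change.** **Recording rule.** Ask the sponsor to confirm the intent, then replace the sentence. If the intent was to count each patient once, suitable wording is: *The first respiratory readmission per patient within 1 year of discharge is recorded, with its date; repeat readmissions are not counted again.* Add that follow-up for death continues after a readmission.

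**Between-arm comparison.** Replace the completers' denominator with all randomised patients by assigned arm, for example the proportion *alive and without respiratory readmission at 1 year*. Deaths in hospital count as failures. State a time origin that exists for every randomised patient, since those who die in hospital have no discharge date, and state how patients with unknown 1-year status are handled.

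**Descriptive report.** Report first respiratory readmission among patients discharged alive as a cumulative incidence at 1 year, with death as a competing event. Label this as descriptive, because being discharged alive is itself determined after randomisation.

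**Cost.** A change of wording and slightly more analysis. The data needed are the dates of readmission and death, which the existing follow-up contacts can supply. The sample size does not change.
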